**Table 2 Tab2:** **Inclusion and exclusion criteria**

**Inclusion criteria**	**Exclusion criteria**
(1) With confirmed infection by the influenza A (H1N1, H3N2) or influenza B virus according to real-time polymerase chain reaction (PCR) or viral culture	(1) Age <18 years or >65 years
	(2) Confirmed bronchitis, pneumonia, pleural effusion and interstitial lung disease *via* chest imaging (radiograph or CT)
(2) Aged 18 to 65 years; axillary temperature ≥38°C and at least two constitutional symptoms (headache, chill, myalgia or fatigue) and one respiratory symptom (cough, sore throat, or rhinitis)	(3) Routine screening tests of blood with leukocyte readings >10.0 × 10^9^/L or neutrophil count ≥80%
	(4) Suppurative tonsillitis or purulent sputum
(3) Illness onset within 36 h	(5) Underling primary disorders such as hematological disease, chronic obstructive pulmonary disease (FEV_1_/FVC <70%, FEV_1_/predicated value <50%; or respiratory failure or right-heart failure), hepatic disease (ALT or AST ≥ triple ULN), renal disease (serum creatinine > 2 mg/dL) or chronic congestive heart failure (NYHA III to IV)
(4) Granting of written informed consent	
	(6) Previous administration of antiviral drugs (amantadine, rimantadine, zanamivir, or oseltamivir phosphate) before disease onset and study enrollment, or administration of traditional Chinese herbal medicine or proprietary Chinese medicine. Administration of BLG granules within 1 week before disease onset
	(7) Allergy to study medication(s)
	(8) Women who are pregnant, or may possibly become pregnant, or who are lactating with a positive urine pregnant test, or with a body mass index (BMI) ≥25 kg/m^2^
	(9) The immunodeficient: malignant tumor; organ or bone-marrow transplantation; AIDS; or taken immune inhibitors during the last 3 months
	(10) Suspicion or history of alcohol/drug abuse
	(11) Participation in another clinical trial <3 months before study randomization
	(12) Acute respiratory infection, otitis, or nasosinusitis 2 weeks before study enrollment
	(13) Vaccination with the influenza vaccine within 6 months
	(14) Other reasons at the investigator’s discretion

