**Table 3 Tab3:** **Termination standards**

**Criteria**	
1	The patient’s illness becomes severe, and the severity meets one of the following criteria: (i) persistent high fever for >3 days (≥39°C); (ii) Severe cough, purulent sputum, bloody sputum, or pectoralgia; (iii) rapid breathing, trouble in breathing, lip cyanosis; (iv) alternation of consciousness (that is, drowsiness, restlessness, convulsions); (v) severe vomiting, diarrhea, dehydration; (vi) imaging confirms signs of pneumonia; (vii) levels of myocardial enzymes, such as creatine kinase (CK), creatine kinase isoenzyme (CK-MB) elevate rapidly; (viii) underlying diseases are exacerbated significantly.
2	Death (including deaths due to influenza and other causes of death)
3	Antibiotic treatment is required (bacterial pneumonia, tympanitis, nasosinusitis secondary to influenza)
4	Serious events occur
5	Other health reasons

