#### Safety evaluation

Safety is evaluated using vital signs, cardiopulmonary signs, adverse reactions, electrocardiography, and clinical laboratory tests (including liver and kidney functions and myocardium enzyme). These indices are compared before and after the drugs were taken.

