#### Statistical analyses

The software used for statistical analyses will be SPSS v17.0 (IBM, Armonk, NY, USA) or SAS v9.2 (SAS Institute, Cary, NC, USA).

All statistical inferences will be determined using two-sided tests. *P* <0.05 will be considered significant, and 95% confidence intervals will be used.

Efficacy analyses will use LOCF to compensate for cases not fully covered during treatment. The LOCF approach uses the last data observed, which is transferred to the database to obtain a complete dataset. The safety assessment will not evaluate missing data.

A comparison between the dropout rate and dropout rate caused by adverse events will be undertaken using the Pearson’s χ^2^test.

Data will be described as the mean, standard deviation, and confidence intervals. If necessary, minimum, maximum, P25, P75, and median values will be provided. Paired measurement data will also show the differences between the mean and standard deviation. When using nonparametric methods, median and mean values will be provided. Count data will be described using the frequency distribution and corresponding percentage. Data of concentrations will be described using the frequency distribution and the corresponding percentage, as well as median and average values. Qualitative information will be described using the positive rate, the number of positive cases, and the denominator.

Baseline data analyses (two sets) will include demographic indicators, as well as general, primary and secondary indicators before intervention. Measurement data will be described using a *t*-test or t’ test (if the variance is absent). Count data will be described using the Pearson’s χ^2^test. Rating data will be described using the two-sample Wilcoxon rank sum test.

With respect to analyses of effectiveness, for quantitative variables, comparisons between groups will be undertaken using repeated measures analysis of variance and covariance analysis. For qualitative variables, comparisons between groups will be tested using the Pearson’s χ^2^test, whereas center effect analysis will use CMH. For rating variables, comparisons between groups will be tested using the Kruskal-Wallis test, regression analysis center effect via the CMH test, or grade logistics.

In terms of center effect analyses, the GLM method will be used for quantitative indicators and CMH methods for qualitative indicators. Rating variables will be evaluated and corrected using a logistic regression model.

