With regard to subgroup analyses, depending on the circumstances, factors that cannot be excluded may have an effect on the prognosis.

For safety analyses, the prevalence of adverse events in the two groups will be compared using the Pearson’s χ^2^test, as well as listing and describing the events that occur during the trial. A description of laboratory test results before and after the test will be described as normal/abnormal changes, as well as the relationship between the abnormal changes and the test drug; these changes will be stated.

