## Discussion

Treatment effectiveness, safety assurance and patient affordability are the key factors for any drugs, including Western medicines and TCHMs. This projected clinical trial will provide evidence as to whether BLG granules are suitable and safe for treating and preventing seasonal influenza.

BLG seems to display a clinical effect during the early onset of illness. Our previous study showed that *IPRS*, clemastanin B and lignin, which are separated from *IIR*, have antiviral roles in the early infection stage of the influenza virus [24-26]. Accordingly, we defined the time of illness onset to be <36 hours. Unfortunately, this criterion made patient recruitment quite difficult. However, this design, which is based on a combination of traditional medical experience and modern pharmacological study, should allow us to discover the objective treatment effectiveness of BLG.

The safety of TCHM is attracting major attention. First, in our study, BLG granules are used only for 5 days in the acute phase, so that it may be safe for humans. Second, we evaluate the safety of BLG based on changes in liver and kidney function after treatment. In addition, western medicines used for treating influenza (such as oseltamivir, which sells for 283 RBM/box in China) is expensive for ‘developing’ countries. Hence, we need to explore new, safe and inexpensive anti-influenza medicine. BLG, which sells for 12.00 RBM/box in China, would be a good choice.

Furthermore, according to basic science studies, the active ingredient of *IIR* also exerts immune-modulating and anti-inflammation effects *in vitro* and *in vivo*. Polysaccharides from *IIR* can promote production of interleukin-2 and interferon-γ, as well as the proliferation of lymphocytes and macrophages in mice [33]. Also, indirubin and its derivatives can suppress the expression of several pro-inflammatory cytokines induced by influenza infection in human macrophages and alveolar epithelial cells [27]. Hence, an evidence-based clinical trial to evaluate the effectiveness of BLG in treating inflammation induced by influenza infection certainly has merit.

In summary, we have described the first clinical trial for treatment using a single herb against influenza A and B viruses in China. We will hold a large-scale clinical trial to comprehensively evaluate the effectiveness and safety of BLG against influenza infection based on the results of this pilot study.

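### The one laboratory-specific analysis sentence summarises results as normal/abnormal changes, which on its own is insensitive to large rises in patients whom the entry criteria admit with abnormal values

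*Protocol article*

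**What the plan says.** The Safety evaluation section names "clinical laboratory tests (including liver and kidney functions and myocardium enzyme") among the safety indices and adds: "These indices are compared before and after the drugs were taken". It gives no method for that comparison.

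The method appears in the safety paragraph of Statistical analyses: "A description of laboratory test results before and after the test will be described as normal/abnormal changes". This is the only analysis sentence specific to laboratory data. Its second half turns to causality and promises, for abnormal changes, a statement of how they relate to the study drug.

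Table 2, exclusion criterion (5), sets the entry limits: "hepatic disease (ALT or AST ≥ triple ULN), renal disease (serum creatinine > 2 mg/dL"). ALT and AST above normal but below 3×ULN are therefore admitted, as is creatinine up to and including 2 mg/dL. Table 2 sets no limit for CK.

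Two more general provisions also bear on the point. Statistical analyses says of data measured before and after: "Paired measurement data will also show the differences between the mean and standard deviation". Evaluation of adverse events counts adverse changes in laboratory indices after enrolment as adverse events and does not require a normal starting value.

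The Discussion states how the safety of Ban-Lan-Gen (BLG) will be judged: "we evaluate the safety of BLG based on changes in liver and kidney function after treatment".

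**The concern.** A normal/abnormal classification discards size. That costs little when every patient enters with normal values, because any important rise must then cross the limit. Here the entry criteria let abnormal values in by design, and in those patients a rise of any size leaves the class unchanged.

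The article does use size elsewhere. Entry is framed in multiples of ULN, and termination criterion 1(vii) in Table 3 refers to how enzymes move: "levels of myocardial enzymes, such as creatine kinase (CK), creatine kinase isoenzyme (CK-MB) elevate rapidly". The laboratory summary drops it.

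At stake is the liver and kidney evidence on which the Discussion rests the safety of BLG. With 59 patients per arm, a hepatic or renal signal would probably appear as a few large individual rises, which is the pattern this summary shows least well.

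**Working it through.** The article gives no figure to reproduce here. The check is mainly one of classification, with three small calculations.

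**Inputs.** The total is 177, allocated 1:1:1 (Number of participants; Design), so 177/3 = 59 per arm. Entry limits are those of Table 2. Table 1 requires laboratory tests at Visit 0 and at Visit 3 (Day 7). The share of patients abnormal at entry and the within-person variation are not in the article and are assumed below.

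**Step 1: classify rises that the entry limits allow.** Call a value abnormal if it exceeds 1×ULN.

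| ALT before → after (×ULN) | Ratio | Class before → after | Change of class |
|---|---|---|---|
| 1.1 → 3.3 | 3.0 | abnormal → abnormal | none |
| 2.0 → 8.0 | 4.0 | abnormal → abnormal | none |
| 2.0 → 10.0 | 5.0 | abnormal → abnormal | none |
| 2.9 → 8.7 | 3.0 | abnormal → abnormal | none |
| 0.98 → 1.02 | 1.04 | normal → abnormal | yes |

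**Step 2: how many patients this could concern.** If a share q starts above the ULN for a given analyte, 59 × q patients per arm cannot show a normal-to-abnormal change. For an assumed q of 5% to 30%, this runs from 59 × 0.05 = 2.95 to 59 × 0.30 = 17.7, or about 3 to 18 per arm.

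**Step 3: does the mean paired difference recover an individual rise?** One patient going from 2 to 8×ULN adds (8 − 2)/59 = 0.10×ULN to the arm's mean change. That is easily overlooked. The maximum would reveal it, but the article promises minimum and maximum only where judged necessary.

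**Step 4: crossings due to ordinary variation.** With no drug effect, the chance of a normal first and an abnormal second reading is p(1 − p), where p is the chance that one lognormal reading exceeds the ULN. For a patient whose true level is 0.9×ULN, an assumed within-person CV of 10% gives 0.145 × 0.855 = 0.12, and a CV of 30% gives 0.36 × 0.64 = 0.23. At a true level of 0.7×ULN the range is 0 to 0.10. Such crossings do occur near the limit, but they are expected equally in all randomised arms.

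**The case against.** A reader might infer that laboratory safety is scored only as normal or abnormal, so that a large rise from an abnormal baseline counts as no change anywhere in the trial. The article does not support that. Under its adverse event definition, ALT going from 2 to 8×ULN can be recorded as an adverse event, graded, assessed for causality, compared between groups and listed. The safety indices are also to be compared before and after treatment without restriction to categories, and paired differences are promised for measurement data in general. All of this stands, and it limits the point to what the laboratory summary shows on its own.

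It does not remove the point. The before/after comparison names no method outside the sentence at issue. Adverse event capture depends on the investigator reporting the change: the article gives no numerical threshold, and Table 4 grades by effect on daily life, so an enzyme rise without symptoms would tend to be graded mild if reported at all. The paired mean dilutes a single rise, as Step 3 shows.

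Two further objections carry weight. First, the wording is loose: in the second half of the sentence, abnormal qualifies the change rather than the value, so a strict two-class table is the natural reading but not the only one. Second, graded shift tables are a detail that a condensed article often leaves to the full protocol or analysis plan. The reply is that the article is not silent: it states a rule, and that rule suits the admitted population poorly.

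It is also tempting to argue that noise across the limit will distort the safety conclusion. That does not follow. The noise does not differ between arms, the summary carries no test, and a multi-analyte noise rate would rest on assumed variances and independent analytes. No such rate is relied on here.

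**Conclusion.** The concern holds in a limited form. The only laboratory-specific analysis sentence describes a summary that, taken alone, is insensitive to large rises in patients already abnormal at baseline, and the entry criteria admit such patients. Other provisions may catch these rises but do not ensure that they are shown by arm.

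The classification result needs no assumption beyond the natural reading of the sentence. The size, about 3 to 18 of 59 per arm for a given analyte, rests wholly on the assumed 5% to 30% abnormal at entry. Whether a given creatinine at or below 2 mg/dL is abnormal depends on the laboratory's own limit, which the article does not state.

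No efficacy conclusion is affected. The change is worth making because it is cheap and bears directly on the stated basis for judging the safety of BLG.

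**What to change.** In the safety paragraph of Statistical analyses, add for ALT, AST, creatinine and CK/CK-MB:

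- a table by arm of baseline category against worst post-baseline category in multiples of ULN, for example ≤1, >1–3, >3–5 and >5;
- a list of every patient whose value at least doubles from baseline and ends above the ULN.

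State that a bare crossing of the limit (≤1 to >1–3 without doubling) is not counted as a notable laboratory change. Keep the normal/abnormal listing as a supplement.

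Applied to the table under Step 1, all four large rises move up at least one category and are listed, since each ratio is 3 or more. The 0.98 to 1.02 case is neither listed nor counted. The two parts complement each other: 1.2 to 2.9×ULN stays in one category but is listed (ratio 2.4), while 2.9 to 5.5×ULN falls short of doubling (ratio 1.9) but moves two categories in the table.

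The cost is one paragraph of wording and a few tables. The values are already required at Visit 0 and Day 7, so no new data are needed. The cut-offs are examples, may need to differ by analyte, and must be fixed before unblinding.

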### Safety and ethics

The drugs used in this clinical trial (BLG granules and oseltamivir) have been approved for clinical use, so there is no potential safety hazard. To ensure that study patients receive effective treatment during rehabilitation, the placebo control group will be provided basic drugs.

Before study commencement, we will explain in detail the research purpose, methods and processes. Satisfactory answers to any questions from the subjects, after obtaining written informed consent, will be included. Also, the center will focus on the purpose, application and execution of the study. Researchers will accept the research plan, treatment procedure, patients, research schedule, CRF and written informed consent. During the trial, the clinical unit must comply with GCP and the scheme of the clinical trial. Pharmaceutical supervisory and administrative departments will occasionally conduct audits and inspections and will cooperate with the sponsor to send medical examiners. Any moderate or serious adverse events will be reported to the Ethics Committee.

## Discussion

Treatment effectiveness, safety assurance and patient affordability are the key factors for any drugs, including Western medicines and TCHMs. This projected clinical trial will provide evidence as to whether BLG granules are suitable and safe for treating and preventing seasonal influenza.

BLG seems to display a clinical effect during the early onset of illness. Our previous study showed that *IPRS*, clemastanin B and lignin, which are separated from *IIR*, have antiviral roles in the early infection stage of the influenza virus [24-26]. Accordingly, we defined the time of illness onset to be <36 hours. Unfortunately, this criterion made patient recruitment quite difficult. However, this design, which is based on a combination of traditional medical experience and modern pharmacological study, should allow us to discover the objective treatment effectiveness of BLG.

The safety of TCHM is attracting major attention. First, in our study, BLG granules are used only for 5 days in the acute phase, so that it may be safe for humans. Second, we evaluate the safety of BLG based on changes in liver and kidney function after treatment. In addition, western medicines used for treating influenza (such as oseltamivir, which sells for 283 RBM/box in China) is expensive for ‘developing’ countries. Hence, we need to explore new, safe and inexpensive anti-influenza medicine. BLG, which sells for 12.00 RBM/box in China, would be a good choice.

Furthermore, according to basic science studies, the active ingredient of *IIR* also exerts immune-modulating and anti-inflammation effects *in vitro* and *in vivo*. Polysaccharides from *IIR* can promote production of interleukin-2 and interferon-γ, as well as the proliferation of lymphocytes and macrophages in mice [33]. Also, indirubin and its derivatives can suppress the expression of several pro-inflammatory cytokines induced by influenza infection in human macrophages and alveolar epithelial cells [27]. Hence, an evidence-based clinical trial to evaluate the effectiveness of BLG in treating inflammation induced by influenza infection certainly has merit.

In summary, we have described the first clinical trial for treatment using a single herb against influenza A and B viruses in China. We will hold a large-scale clinical trial to comprehensively evaluate the effectiveness and safety of BLG against influenza infection based on the results of this pilot study.

## Trial status

This clinical trial was reviewed by the Ethics Committee of the First Affiliated Hospital of Guangzhou Medical University at the end of 2011. The first patient was enrolled in 2012. From early 2012 to 2014 in June, 50 patients had finished the treatment and observation cycle. This clinical trial is expected to be completed at the end of 2015.

## Abbreviations

AUC: area under the curve
BMI: body mass index
CRF: case report form
CK: creatine kinase
CK-MB: creatine kinase isoenzyme
GCP: good clinical practice
HA: hemagglutinin
IIR: *Isatis indigotica* root
ILI: influenza-like illness
IRPS: *Isatis indigotica* root polysaccharide
ITTP: intent-to-treat population
LOCF: last observation carried forward
MITTP: modified intent-to-treat population
NA: neuraminidase
PPP: per-protocol population
SAP: safety analysis population
TCHM: Traditional Chinese herbal medicine
